## Abstract

**Introduction:**

Adalimumab is effective for maintenance of remission in patients with Crohn’s disease (CD) at a dose of 40 mg subcutaneously every 2 weeks. However, adalimumab is associated with (long-term) adverse events and is costly. The aim of this study is to demonstrate non-inferiority and cost-effectiveness of disease activity guided adalimumab interval lengthening compared to standard dosing of every other week (EOW).

**Methods and analysis:**

The Lengthening Adalimumab Dosing Interval (LADI) study is a pragmatic, multicentre, open label, randomised controlled non-inferiority trial. Non-inferiority is reached if the difference in cumulative incidence of persistent (>8 weeks) flares does not exceed the non-inferiority margin of 15%. 174 CD patients on adalimumab maintenance therapy in long-term (>9 months) clinical and biochemical remission will be included (C-reactive protein (CRP) <10 mg/L, faecal calprotectin (FC) <150 µg/g, Harvey-Bradshaw Index (HBI) <5). Patients will be randomised 2:1 into the intervention (adalimumab interval lengthening) or control group (adalimumab EOW). The intervention group will lengthen the adalimumab administration interval to every 3 weeks, and after 24 weeks to every 4 weeks. Clinical and biochemical disease activity will be monitored every 12 weeks by physician global assessment, HBI, CRP and FC. In case of disease flare, dosing will be increased. A flare is defined as two of three of the following criteria; FC>250 µg/g, CRP≥10 mg/l, HBI≥5. Secondary outcomes include cumulative incidence of transient flares, adverse events, predictors for successful dose reduction and cost-effectiveness.

**Ethics and dissemination:**

The study is approved by the Medical Ethics Committee Arnhem-Nijmegen, the Netherlands (registration number NL58948.091.16). Results will be published in peer-reviewed journals and presented at international conferences.

**Trial registration numbers:**

EudraCT registry (2016-003321-42); Clinicaltrials.gov registry (NCT03172377); Dutch trial registry (NTRID6417).

Strengths and limitations of this studyThe Lengthening Adalimumab Dosing Interval (LADI) study is the first randomised controlled trial that investigates adalimumab interval lengthening in Crohn’s disease patients.This pragmatic study is clinically relevant and results can easily be implemented in daily practice.The National Crohn and colitis patients organisation is involved and patient-reported outcomes are included.The study is not blinded.

## Background

Crohn’s disease (CD) is a chronic inflammatory disease of the gastrointestinal tract, characterised by a relapsing and remitting disease course. Patients show an abnormal mucosal immune response, resulting from an interplay of genetic susceptibility, environmental factors and the intestinal microflora.^1^ Treatment consists of immunosuppressive medication, including monoclonal antibodies that block tumour necrosis factor alpha (anti-TNF); such as infliximab, adalimumab and certolizumab. Adalimumab is a humanised anti-TNF antibody that is effective as both induction and maintenance therapy for CD.^2–4^ Adalimumab is administered by subcutaneous (sc) injection and an induction dose of 80 mg (week 0) and 40 mg (week 2) or 160 mg (week 0) and 80 mg (week 2) are generally used, followed by 40 mg every 2 weeks.^5^

Although adalimumab is generally safe, side effects do occur. The risk of (opportunistic) infections is increased, especially in combination with immunosuppressive therapies, most often thiopurines or methotrexate.^6–9^ A recently published review on long term safety of adalimumab (n=3606 CD patients) showed a high absolute risk of any infection of 119 events per 100 patient years (PYs) and a risk of serious infection of 6.7/100 PYs in this selected trial-population with relatively low comorbidity.^10^ The incidence rate of injection site reactions (local pain and swelling) was 7.7/100 PYs.^10^ In addition, several reports show an increased risk of skin cancer (both melanoma and non-melanoma skin cancer), especially in combination with thiopurines.^6 7 9 11 12^ In addition to potential side effects, the costs of adalimumab are significant. Before the introduction of biosimilars, the costs of anti-TNF in the Netherlands were €15 000–30 000 per CD patient annually.^13 14^ Anti-TNF including adalimumab is expected to continue to be the main cost driver of CD management for several reasons. First, the number of CD patients is increasing in the Netherlands.^15^ Second, recent data stimulate an early use of anti-TNF with an accelerated step-up or top-down approach in combination with treat-to-target (mucosal healing), to prevent bowel damage.^16^ Third, the entry of lower cost biosimilars will possibly cause physicians to preferentially prescribe anti-TNF treatment, which will increase its use.^17–19^

Discontinuation of adalimumab therapy in CD patients in stable clinical remission is a clinical strategy that may aid in reducing the risk of side effects, costs and avoid prolonged immunosuppression during a quiescent disease course. However, in a large meta-analysis on individual patient data (n=1330, including the landmark study by Louis *et al*
20) on cessation of anti-TNF therapy, approximately 38% of the patients had a relapse in 1 year, and 52% after 2 years of follow-up (Pauwels *et al*, unpublished data). Therefore, an alternative strategy of dose reduction of adalimumab rather than discontinuation may be considered. In rheumatoid arthritis (RA), the Dose REduction Strategy of Subcutaneous TNF inhibitors (DRESS) study concluded that disease activity guided dose reduction of anti-TNF is non-inferior and cost-effective, compared with maintaining regular dosing.^21 22^ However, extrapolation of these results to CD is questionable, since RA patients generally use different concomitant medication, suffer from different comorbidities and anti-TNF shows different pharmacodynamic characteristics in RA patients.^23 24^ In CD, adalimumab dose reduction is uncommon in daily practice. Only two retrospective cohort studies (n=46+40) reported CD patients who used adalimumab 40 mg every 3 weeks (ETW).^25 26^ After a median follow-up of 16 and 24 months, respectively 63% and 65% remained in clinical remission.

The aim of this randomised controlled trial is to demonstrate non-inferiority and cost-effectiveness of disease activity guided adalimumab injection interval lengthening compared with standard of care (continued every other week (EOW) dosing) in maintaining remission in CD. In this paper we describe the study design as well as potential pitfalls and outcomes.

## Objective

### Primary objective

To demonstrate non-inferiority of disease activity guided adalimumab injection interval lengthening compared with adalimumab EOW dosing (standard of care) in CD patients in stable disease remission at 48 weeks of follow-up. Non-inferiority is reached if the difference in cumulative incidence of persistent flares not exceeds the non-inferiority margin of 15%. A persistent flare is defined as two of three of the following criteria, persisting for >8 weeks despite dose escalation of adalimumab:Faecal calprotectin (FC) >250 µg/g.C-reactive protein (CRP) ≥10 mg/L.Harvey-Bradshaw Index (HBI) ≥5.

### Secondary objectives

To report the proportion of patients that had successful interval lengthening, defined as the absence of a disease flare, while treated with adalimumab ETW or every 4 weeks (EFW), at week 48.To identify factors that are associated with successful interval lengthening (eg, baseline patient and treatment characteristics, FC, CRP, adalimumab drug levels and antibodies to adalimumab).To compare the cumulative incidence of patients with a transient flare (duration ≤8 weeks) between the intervention and control group at week 48.To compare the proportion of patients that used budesonide, prednisone or other immunomodulators in order to treat a (transient) flare.To compare the proportion of patients in clinical and biochemical remission between the intervention and control group at week 48. Remission is defined as an HBI <5, FC <150 µg/g and CRP <10 mg/L. In case disease activity is assessed with endoscopy or MRI scan, that conclusion overrules our definition.To compare inflammatory bowel disease (IBD)-specific quality of life by the Short-IBD Questionnaire (SIBDQ)) between the intervention and control group every 12 weeks during follow-up.To compare disease activity by HBI and patient reported outcome (PRO-2) between the intervention and control group every 12 weeks during follow-up.To compare medical consumption (by institute for Medical Technology Assessment (iMTA) Medical Consumption Questionnaire (MCQ)) and work productivity (by iMTA Productivity Cost Questionnaire (PCQ)) between the intervention and control group until week 48, in order to calculate the decremental cost-effectiveness ratio of this interval lengthening strategy.To compare the rates of (serious) adverse events ((S)AEs) that are (possibly) related to adalimumab and the rates of (S)AEs that are (possibly) related to adalimumab interval lengthening between the intervention and control group, expressed as events/100 PYs of follow-up.To compare adalimumab use between the intervention and control group, including the cumulative dose during follow-up, the proportion of patients that uses adalimumab ETW and EFW.

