### Inclusion and exclusion criteria

All adult CD patients with colonic and/or distal ileal and/or proximal CD, who are treated with adalimumab 40 mg every 2 weeks at a stable dose, at least 9 months in steroid-free clinical remission and not scheduled for CD-related surgery, are eligible for participation.^28^ Remission is defined as an HBI <5, FC <150 µg/g and CRP <10 mg/L. The current guidelines from the European Crohn’s and Colitis Organisation (ECCO) suggest to use CRP <10 mg/L for the definition of disease remission.^5^ Endoscopic assessment prior to enrolment is not mandatory, however if an ileocolonoscopy was performed before the start of the study and demonstrated complete mucosal healing (Simple Endoscopic Score-CD <3 or no ulcerations), an FC <250 µg/g is accepted as inclusion criterium. Permitted concomitant CD therapies are: aminosalicylates, azathioprine, 6-mercatopurine, methotrexate and thioguanine at a stable dose for 12 weeks. Patients with arthralgia will be included, however inflammatory arthritis is an exclusion criterium, as this can provide elevated inflammatory markers. Furthermore, patients with active draining fistulas are excluded. Other exclusion criteria are pregnancy or lactation and other significant medical conditions that might interfere with this study (such as a current/recent malignancy, immunodeficiency syndromes and psychiatric illness), or when it is to be expected that the outcome cannot be measured (short life expectancy, planned major surgery, language issues).

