### Cointervention

The use of previously mentioned concomitant medication is allowed and must be documented on the case-report form (CRF) (stating type, dosage and duration). If possible, existing concomitant medication should not be changed during the study.

If patients experience worsening of symptoms in between visits, they must contact the outpatient clinic. For further treatment of the flare, patients in the control arm are referred to their treating physician. In the intervention arm, patients will return to the preceding effective adalimumab dosing interval (figure 1). The decision to start concomitant therapy remains at the discretion of the treating physician.

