We decided to assess non-inferiority with regard to persistent flares (persisting >8 weeks independent of treatment changes such as adalimumab dose escalation) since these are the most relevant clinical outcomes in this setting. Temporary flares (persisting <8 weeks) that resolve after appropriate treatment are less difficult to manage and are likely to occur as an acceptable result of searching for the optimal individualised treatment interval. Temporary flares will still function as relevant secondary outcome in our trial. For the definition of a flare, two consecutive measurements demonstrating two out of three of the following criteria; FC >250 µg/g, CRP ≥10 mg/L, HBI ≥5 are required. As it has been shown that flares are frequently temporary and occur and sometimes disappear without regimen change, a flare is only considered a flare if it is confirmed two times. For this composite endpoint we preferred to incorporate the HBI instead of the Crohn’s Disease Activity Index on account of accessible clinical implementation in daily practice. In addition, FC and CRP are non-invasive, cheap and widely available biomarkers of disease activity.^42^ Furthermore, FC correlates to endoscopic disease activity.^43 44^ Recently, it was shown that an increase in FC can precede on the onset of clinical symptoms.^45^ Indeed, due to our definition of a flare, patients without clinical symptoms can also fulfil the definition of a (biochemical) flare. In addition, the requirement of an elevation in inflammatory markers at two time points allows for the exclusion of confounders such as *Clostridium difficile* infection and use of ‘non-steroidal anti-inflammatory drugs’ (NSAIDs).

We decided not to include endoscopy outcomes in the inclusion criteria or primary endpoint. An endoscopic procedure is a burden for patients due to the invasive procedure and the intensive preparation. In addition, we aimed for study results that may be easily implemented in daily practice. Instead of an endoscopy, we used a combination of surrogate markers of inflammation including HBI, CRP and FC to determine clinical remission. A protocolised treatment is advised when a flare occurs (figure 1). However, treatment choices are not mandatory and bridging therapy (including steroids) is left to the discretion of the treating physician.

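### Week-48 remission is judged without regard to steroid use, although entry requires steroid-free remission and steroids may be given during follow-up

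*Protocol article*

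**What the plan says.** All references are to the protocol article.

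- **Entry** (Inclusion and exclusion criteria): patients must be "at least 9 months in steroid-free clinical remission". The three remission thresholds follow in the next sentence.
- **Week-48 remission** (Secondary objectives): "Remission is defined as an HBI <5, FC <150 µg/g and CRP <10 mg/L". One override is given: "In case disease activity is assessed with endoscopy or MRI scan, that conclusion overrules our definition". Steroid use is not mentioned.
- **Successful interval lengthening** (Secondary objectives): "defined as the absence of a disease flare, while treated with adalimumab ETW or every 4 weeks (EFW), at week 48". Again there is no steroid condition.
- **Steroids during follow-up**: the Discussion says that "bridging therapy (including steroids) is left to the discretion of the treating physician", and Cointervention says "The decision to start concomitant therapy remains at the discretion of the treating physician".
- **Steroid use as its own outcome** (Secondary objectives): "To compare the proportion of patients that used budesonide, prednisone or other immunomodulators in order to treat a (transient) flare".
- **Data collected** (Table 1): concomitant medication is recorded at week 0 and at every six-weekly contact, including week 48.

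**The concern.** The trial asks whether patients who entered in stable remission stay there on fewer injections. The week-48 remission comparison is the secondary outcome that speaks to this most directly. Steroids can lower all three components of the definition, so a patient can meet it because of a steroid course and not because the adalimumab interval is sufficient. The outcome then measures a weaker state than the one patients had at entry.

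If steroid use at week 48 differs between arms, the remission difference is distorted as well as the level. The same gap exists in the definition of successful interval lengthening, although there its extent depends on how the words are read.

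This is not a detail that an article leaves to the full protocol or the analysis plan. The definition is written out with its thresholds and its override, and steroid status is absent from it.

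**Working it through.** The point rests on no stated figure, so there is none to reproduce. The check compares definitions and then illustrates size on assumed rates.

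**Step 1: the definitions side by side**

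| | Three thresholds | Steroid condition | Other condition |
|---|---|---|---|
| Entry | yes (calprotectin relaxed to below 250 µg/g after documented mucosal healing) | steroid-free, at least 9 months | stable dose every 2 weeks |
| Week-48 remission | yes | none | endoscopy or MRI overrules |
| Successful lengthening | not used; absence of flare | none | on a 3- or 4-week interval |

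**Step 2: can the case arise under the protocol's own rules?** Take a patient on the 4-week interval who flares at about week 40.

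- Step 3 of the intervention returns a confirmed flare to the preceding interval, here 3 weeks, which is still a lengthened interval.
- The physician may add a steroid.
- The Figure 1 legend places reassessment 6 to 8 weeks after the start of the possible flare: 40 + 6 = 46 to 40 + 8 = 48.
- If index and markers are normal on the steroid at week 48, the patient is in remission by definition.
- Under Assessments, monitoring beyond week 48 is for patients in flare at that visit, so a relapse after the steroid is stopped would not be captured.

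A control patient given steroids late in follow-up is classified the same way.

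**Step 3: does this patient also count as a successful lengthening?** That depends on the meaning of week 48 in the success definition.

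- *State at the visit:* yes. The patient is on a 3-week interval and not in flare.
- *No flare through week 48:* no. The week-40 flare excludes the patient.
- *Either reading:* a patient given steroids for symptoms never confirmed as a flare can still count, because the Discussion requires a flare to be confirmed twice.

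**Step 4: size, on assumptions only.** The documents give no steroid rates and no expected remission proportion. Let *r* be the proportion meeting the week-48 definition, assumed to be 70% in both arms, and let *s* be the share of those patients on steroids. Then:

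steroid-free difference = r(1 − s_I) − r(1 − s_C)

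The planned 174 patients split 2:1 into 116 and 58, so 0.70 × 116 = 81.2 and 0.70 × 58 = 40.6 meet the definition. The difference as defined is 0 in every row.

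| s_I | s_C | Reclassified, intervention | Reclassified, control | Steroid-free difference |
|---|---|---|---|---|
| 5% | 2% | 81.2 × 0.05 = 4.1 | 40.6 × 0.02 = 0.8 | 0.665 − 0.686 = −2.1 points |
| 10% | 3% | 8.1 | 1.2 | 0.630 − 0.679 = −4.9 points |
| 15% | 5% | 12.2 | 2.0 | 0.595 − 0.665 = −7.0 points |
| 5% | 5% | 4.1 | 2.0 | 0.665 − 0.665 = 0 |
| 2% | 5% | 1.6 | 2.0 | 0.686 − 0.665 = +2.1 points |

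The last two rows matter as much as the first three. With equal use, only the level falls, by 0.70 × 0.05 = 3.5 points in each arm. With more use among controls, the sign reverses.

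**The case against.** Several points on the other side are fair.

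- **There is no internal contradiction.** The article uses the same three thresholds for remission at entry and at week 48; steroid-free is an added eligibility condition. A reader might infer that the article contradicts itself or removed a condition it had set. The text does not support that. What stands is that the outcome is weaker than the entry state.
- **Steroid use is compared between arms.** This makes an imbalance visible. It is, however, one proportion per arm for use at any time to treat a flare. It does not identify who was on steroids with normal markers at week 48, so it cannot correct the remission outcome.
- **The direction is not established.** A reader might infer that the definition favours lengthening. A flare in the intervention arm can be met by returning to a shorter interval, whereas controls are already on the 2-week interval and are referred to their physician. Steroid use per flare could be higher among controls.
- **The success proportion need not be inflated.** A reader might infer that it is inflated like remission and that this carries into the prediction model. The first holds for patients with a confirmed flare only on the visit-state reading. As for the second, the model under Planned data analysis predicts a persistent flare, although the secondary objective speaks of factors for success.
- **Only secondary outcomes are involved.** That is correct. The persistent-flare endpoint, the margin and the sample size are untouched.

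**Conclusion.** The point holds for week-48 remission: as written, a patient with normal index and markers on prednisone or budesonide counts as in remission unless endoscopy or MRI says otherwise. This follows from the text and needs no assumption about rates.

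For successful interval lengthening the point is narrower. The definition leaves open whether absence of flare applies throughout or at the visit, and on either reading it does not exclude a patient on steroids at week 48.

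Direction and size are unknown. The shifts of −7.0 to +2.1 points rest entirely on the assumed 70% remission proportion and the assumed steroid shares. They show what such shares would do and are not estimates for this trial. The change is worth making because it is cheap and brings the outcome closer to the state the trial aims to maintain.

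**What to change.** 1. **Week-48 remission.** Keep the three thresholds and the imaging override, and add that no systemic steroid or budesonide for Crohn's disease is in use at week 48. Report the marker-only version alongside. Limiting the condition to Crohn's disease avoids counting steroids taken for other reasons as failure.
2. **Successful interval lengthening.** Keep the existing requirement of no flare on the 3- or 4-week interval. State whether it applies through week 48 or only at the visit. Add that patients on steroids for Crohn's disease at week 48 are not successes. Do not replace the definition with a state at week 48: that would admit patients who flared on the 4-week interval, returned to 3 weeks and had finished steroids, and could raise the proportion.
3. **Data.** Use the concomitant medication already recorded at week 48, and confirm that the case report form captures indication and dates for steroids.

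No new visit or test is needed, and nothing changes in who may receive steroids; only the classification of outcomes changes. The cost is wording and slightly lower reported proportions. The condition does not reproduce the nine steroid-free months required at entry: a patient who stopped shortly before the visit would still pass. That limit should be stated with the result.

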### Study groups

#### Control group

The control group continues maintenance treatment with adalimumab sc 40 mg EOW. Treatment decisions are made at the discretion of the treating physician. Of note, dose reduction beyond 40 mg per 2 weeks is currently not recommended according to national guidelines.^29^ Patients follow a standardised protocol based on the tight control/treat-to-target principle in order to maintain low disease activity.^16^

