#### Safety

AEs and SAEs are registered during follow-up. All SAEs are reported to the METC Arnhem-Nijmegen.

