### Randomisation, allocation concealment, stratification

Patients are randomised by the research physician using a computer-generated randomisation system (Castor). Castor uses a validated variable block randomisation model with block sizes of 6, 9 and 12. Patients will be randomised in a 2:1 ratio for the intervention or the control group, respectively. We chose 2:1 randomisation to stimulate patient inclusion, as patients have a higher chance to randomise for the intervention group. Furthermore, more determinants can be included in a prediction model for successful dose reduction if the intervention group is larger. Patients will be stratified on comedication use (yes/no), as the incidence of flares could possibly be different with or without comedication use. Comedication includes azathioprine, 6-mercaptopurine, 6-thioguanine, methotrexate. Both patients and physicians are un blinded, as we aim to represent daily practice during this pragmatic study.

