### Planned data analysis

The primary outcome; cumulative incidence of persistent flares will be expressed as proportions in both groups. A CI for the difference between study groups will be determined (adjusted for comedication use at baseline using the Cochran-Mantel-Haenszel procedure, as this variable is used for stratification in the randomisation process).^37^ The upper limit of the CI will be compared with the non-inferiority margin. We will use both intention to treat and per protocol analyses, as the latter is considered the most conservative analysis for non-inferiority trials.^38^ Patients in the interval lengthening group are included in the per protocol analyses if they: lengthened the adalimumab interval at least to 3 weeks, regardless whether they returned to a preceding effective interval in case of a disease flare. Patients in the control group are included in the per protocol analyses if they: used adalimumab EOW without consistent interval lengthening, incidental postponement of an injection during infection or around holidays is allowed. Descriptive patient (and treatment) baseline variables will be summarised as means±SD, medians with IQRs or percentages, depending on the type of measurement. Gender, body mass index, age, prior medication for CD, disease duration, Montreal classification, IBD-related surgical history, comorbidity, inflammatory parameters including HBI, FC, CRP, adalimumab drug levels and antibodies to adalimumab will be reported.

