The secondary continuous outcomes HBI, SIBDQ, PRO-2, adalimumab drug levels and antibody levels at 48 weeks will be analysed by either Student’s t-test or Mann-Whitney U test depending on the type of distribution of the data. In addition, the course over time for several continuous outcomes measured at multiple time points (every 12 weeks) will be analysed using repeated measures analyses in which the outcome can be corrected for the baseline value of the specific outcome and potential confounding factors. The number of (S)AEs that are (possibly) related to adalimumab or to adalimumab interval lengthening will be reported as rates, defined as events/100 PYs of follow-up; details of these (S)AEs will be provided. In the intervention group, patient characteristics and clinical features will be analysed to predict a persistent flare. A prediction model will be developed and fitted using a univariable selection based on a p value <0.2 and a multivariable approach with backward selection. Predictive accuracy will be determined by the area under the receiver operating curve. A two-sided p value of <0.05 is considered statistically significant. All statistical analyses will be performed by using IBM SPS Statistics V.25.0.

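### The between-arm safety comparison is limited to events attributed to adalimumab or to interval lengthening, so one contrast says little and the other depends on open-label causality judgement

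*Protocol article*

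**What the plan says.** The protocol article, under Secondary objectives, sets out two safety comparisons per 100 patient-years. The first is "To compare the rates of (serious) adverse events ((S)AEs) that are (possibly) related to adalimumab". The second is the "rates of (S)AEs that are (possibly) related to adalimumab interval lengthening between the intervention and control group". Planned data analysis repeats the restriction: "The number of (S)AEs that are (possibly) related to adalimumab or to adalimumab interval lengthening will be reported as rates", with details promised for those events only.

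Collection is wider than analysis. Under Safety, "AEs and SAEs are registered during follow-up", with no relatedness filter, and Table 1 schedules adverse events at every six-weekly contact in both arms.

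On assignment, "The control group continues maintenance treatment with adalimumab sc 40 mg EOW". The per protocol definition for controls requires that they "used adalimumab EOW without consistent interval lengthening, incidental postponement of an injection during infection or around holidays is allowed". On blinding, "Both patients and physicians are un blinded, as we aim to represent daily practice during this pragmatic study". The article does not say who judges relatedness and describes no blinded assessment of it.

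**The concern.** Randomisation protects a comparison of events that are counted in the same way in both arms. Both stated comparisons first pass events through a causality judgement that can depend on the arm.

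For lengthening-related events, the label presupposes the intervention. A hospital admission might be counted as lengthening-related in a patient on the longer interval, while the same admission in a control would have almost no route into the count.

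For adalimumab-related events, both arms can contribute, but the treatment is known. Someone who knows that a patient receives less drug may be slower to blame the drug. That would make lengthening look safer than it is.

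At stake is a secondary claim that carries weight. Fewer side effects is part of the reason for choosing a non-inferiority design (Design section). A possible reduction in side effects is also one of three benefits weighed against the 15% margin (Sample size section), beside fewer injections and lower cost.

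**Working it through.** The article states no figure for the safety comparison, so there is none to reproduce. The check takes each contrast in turn and uses the article's own numbers to give it scale.

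**Inputs**
- 174 patients randomised 2:1 (Sample size): 174 × 2/3 = 116 intervention, 174 × 1/3 = 58 control.
- Follow-up 48 weeks (Intervention group section).
- Background rate of any infection, 119 per 100 patient-years (Background). It serves only as an example of a frequent event.
- Attribution probabilities: not in the article, therefore assumed and shown over a range.

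**Person-time, assuming complete follow-up**
- Intervention: 116 × 48/52 = 107.1 patient-years.
- Control: 58 × 48/52 = 53.5 patient-years (53.54, about 54).

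**Contrast 1: lengthening-related events.** Controls are assigned to the standard interval, so their count is near zero whatever the true safety of the two strategies. With k events in the intervention arm and none in controls, the rate difference is 100 × k/107.1, which is simply the intervention rate. For example, k = 9 gives 8.4 per 100 patient-years. No randomised control rate is being subtracted in any useful sense.

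**Contrast 2: adalimumab-related events.** Let λ be the true event rate, the same in both arms, and let p_I and p_C be the probabilities that an event is called related. The attributed rates are λ × p_I and λ × p_C, and the apparent rate ratio is

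(λ × p_I)/(λ × p_C) = p_I/p_C.

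The background rate and the person-time cancel, so drop-out that is equal in the two arms does not change the ratio. Before attribution, the expected infections are 107.1 × 1.19 = 127 and 53.54 × 1.19 = 64.

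| Assumed p_I vs p_C | Attributed rates per 100 patient-years | Apparent rate ratio (true value 1) |
|---|---|---|
| 40% vs 50% | 47.6 vs 59.5 | 0.80 |
| 25% vs 30% | 29.75 vs 35.7 | 0.83 |
| 20% vs 30% | 23.8 vs 35.7 | 0.67 |
| 20% vs 40% | 23.8 vs 47.6 | 0.50 |

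With equal attribution the ratio is 1. If attribution were more frequent in the intervention arm, the ratio would exceed 1, so the direction is not certain.

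**Does the article's defence of the open label cover this?** The Discussion recognises attribution bias and accepts it because it should not make dose reduction look better than it is. Its example is flares being reported sooner in patients on a reduced dose. Under-attribution of side effects to a reduced dose runs the other way and favours lengthening, so that argument does not reach it.

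**The case against.** Several objections have force.

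- *A full protocol or SAP may add an all-event comparison.* It may, and the absence of one here is not the point. The point is that the comparison the article does state, in both the objective and the analysis section, is filtered on attribution.
- *The assessor is not named.* Correct. A reader might infer that unblinded treating physicians judge relatedness. The article says only that patients and physicians are unblinded. A data safety monitoring board independently assesses safety (Design section), but it is not described as adjudicating causality.
- *Lengthening-related events are not impossible in controls, and the comparison is not undefined.* Also correct. The per protocol definition foresees controls who lengthen consistently or postpone an injection. The control rate and the difference are defined; only a ratio would fail if the control count were exactly zero. What remains is that the contrast carries little information.
- *No test is specified for adverse event rates.* True: they are to be reported as rates. A stated chance of a false significant result would rest on a test supplied by the reader and on one assumed attribution pair, so none is claimed here.
- *The trial can still estimate relative safety without bias from attribution.* It can, because all events are registered. It would be wrong to infer that the data are inadequate; the weakness lies in the stated analysis.
- *The choice of 15% does not rest on safety alone.* Agreed. The Design section concerns the type of design and not the margin. The Sample size section lists three benefits and also cites another trial's margin, study-group discussion and the funder's approval.

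**Conclusion.** The point holds in limited form. The lengthening-related contrast is close to uninformative because its control rate is near zero by design. The adalimumab-related contrast is open to differential attribution, and the direction that favours lengthening is not addressed in the article.

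The illustrated ratios of 0.50 to 0.83 assume equal true rates and the attribution pairs shown. They indicate what modest to large differences in judgement could produce and do not predict what will happen. The existence of the weakness does not depend on them. It depends on the attribution filter, the open label and the absence of a described blinded assessor.

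This concerns a secondary objective. The non-inferiority conclusion on persistent flares is not affected.

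**What to change.** In Secondary objectives and Planned data analysis, make the between-arm safety comparison all AEs and all SAEs (and, for example, all infections) per 100 patient-years, regardless of attribution. Give a rate ratio or rate difference with its 95% CI. Report adalimumab-related events by arm descriptively. Report lengthening-related events descriptively for the intervention arm only. The choice of rate model can be left to the SAP.

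The cost is wording: the events are already recorded at every contact in both arms. The small downside is that counting unrelated events may dilute a true drug-related difference, which is why the attributed rates should stay as supportive information.
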